### Standards of peri-operative care

Patients will be required to abstain from smoking and alcohol for 1 month pre-operatively. Supplemental enteral nutrition will be given to patients who have lost >10% of their baseline body mass and all patients will receive 7 days of pre-operative immunonutrition by Oral Impact® independent of their nutritional status [19].

All patients will receive appropriate antibiotic prophylaxis at induction of anaesthesia and post-operative analgesia will be by patient controlled epidural analgesia (PCEA) or alternatively by standard patient controlled analgesia (PCA). Post-operative nutrition will be commenced on day 2 or 3 post-operation via the jejunostomy and at an initial low volume (250 mls) and increased incrementally. Deep vein prophylaxis will be administered routinely by low molecular weight heparin. Chest physiotherapy and post-operative incentive spirometry will be standard for all patients. In cases where an anastomotic leak is suspected the investigation of reference will be an upper gastro-intestinal endoscopy, or alternatively a CT scan with both injection and ingestion of contrast medium.

### Histological analysis

Pathological examination of the operative specimen must report upon: tumour location, type of operation, details of lymphadenectomy and detailed description or lymph node stations, a macroscopic tumour description, definitive histological classification, documentation of the % of signet ring type cells, Lauren classification, definitive results of per-operative frozen sections, pTNM/ypTNM stage according to the 2009 7th edition of the UICC classification for gastric cancers, resection radicality (R0, R1, R2) and documentation of histological tumour response after neoadjuvant chemotherapy.

### Patient follow-Up after surgery

Participating patients will be reviewed in out-patients 1 month (+/−7 days) after hospital discharge. They will have a full clinical examination. Questionnaires will be completed with regards to quality of life (QoL), emotional state, emotional adjustment, perception of illness and lifestyle burden. A further consultation will be scheduled for one month (+/−7days) after completion of adjuvant chemotherapy with evaluation of clinical state, treatment tolerance, haematological parameters, renal function, tumour markers, evaluation of cardiac ejection fraction after Epirubicin by echocardiogram and the same set of questionnaires will be completed.

All participants will subsequently be followed for 3 years after randomisation. Out-patient consultations will be scheduled every 4 months (+/−15 days) and patients will be evaluated by clinical examination, thoraco-abdominal CT scan, tumour marker estimation (CEA and CA19.9) and QoL questionnaires. Further examinations will be requested as required. If disease recurrence is suspected its site (loco regional or distant) must be documented by the appropriate investigations and histological proof be obtained wherever possible. In cases of strong clinical suspicion of recurrence without radiological or histological proof, surgical exploration is recommended to identify peritoneal carcinomatosis not visualised by standard radiological investigation. All cases of disease recurrence will be discussed at the multi-disciplinary team meeting and further therapeutic strategies recorded.

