To support these observations and establish more reliable data regarding the behaviour of SRC tumours, at the start of 2010 our team launched a French retrospective multicenter study of all consecutive oesophagogastric adenocarcinomas in 19 centres in France treated between January 1997 and January 2010 (ADCI001) [8]. Amongst 3010 patients registered 1050 (34.9%) had a SRC tumour, with 126 being metastatic at diagnosis and excluded from the study. The remaining 924 patients underwent an intention to treat analysis according to whether they underwent primary surgery (n = 753, 81.5%) or neoadjuvant chemotherapy (n = 171, 18.5%). Multivariate analysis showed pre-operative chemotherapy to be an independent predictor of poor survival (HR = 1.4, 95% CI 1.1-1.9, p = 0.042), with overall survival at 2 years of 27.1% in the primary surgery group versus 12.3% in patients treated with neoadjuvant chemotherapy. Hence, increasingly data is suggestive of SRC chemo resistance, and a deleterious effect of delaying definitive surgery for an ineffective treatment whose toxicity may cause host immunosuppression facilitating disease progression.

There is therefore clear impetus for a prospective randomised study to evaluate the appropriate perioperative therapeutic strategy for SRCs.

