### Statistical evaluation and sample size calculation

Phase II– The phase II part of this trial will determine the percentage of patients in the experimental limb of the study (group B) who are alive at 24 months and thus validate the interest pursuing the evaluation of a strategy of primary surgery in a subsequent phase III trial. To demonstrate the interest of the experimental arm of this study, it will be necessary to include 40 in each treatment arm, with a unilateral alpha error of 5% and a power of 85%. Taking into account a 5% level of loss to follow-up, 84 patients will be included in total (42 in each treatment arm). If 7 or less patients are alive after 24 months, then the treatment B will be considered not interesting. Survival data for patients from phase II of this trial will allow for the readjustment of the number of patients required to be enrolled in the phase III trial according to the adaptive trial design.

Phase III – The objective of the phase III trial will be to demonstrate the superiority of group B and the principal outcome criteria will be overall survival. To demonstrate a desired 10% difference in overall survival in favour of group B at 24 months, with a bilateral alpha error of 5% and a power of 85%, it will be necessary to observe 291 deaths. With an estimated rate of inclusion of 6 patients per month, with a 5% rate of loss to follow-up and surveillance of the last included patient of 24 months, a total of 314 patients will have to be recruited. On this basis 230 additional patients will need to be recruited after the completion of phase II.

Two intermediate analyses are planned, one for Phase III sample size read justement and the second one to allow for the early identification of the superiority of group B. The first intermediate analysis of survival data will take place at the end of phase II. The second intermediate analysis will be performed after either 175 deaths or 60% of events have occurred.

Statistical analysis for phase II will be performed on a modified intention to treat population meaning all patients who can be evaluated and who are not lost to follow up at 24 months. For phase III, analysis of the main criteria will be performed on an intention to treat (ITT) principle. The per-protocol population will be defined as the ITT population having no major deviation or major of the protocol.

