Recently Messager et al [8] have published the results of a large multicentre comparative cohort study investigating the impact of peri-operative chemotherapy on survival in patients with SRC gastric tumours. It represents the largest study conducted on this histological subtype and involved analysis of 1050 patients diagnosed with SRC gastric tumours. No survival benefit was demonstrated for patients with SRC histology receiving peri-operative chemotherapy. Nor did neoadjuvant therapy result in tumour down-staging, down-staging of nodal disease, or decrease the disease recurrence. Indeed the authors found some evidence that disease progression during neoadjuvant treatment may have occurred in this subgroup of patients - extended resections were more commonly required and a longer median survival for patients treated with surgery alone prior to the incorporation of peri-oerative chemotherapy into the French guidelines for GA in 2006. This provides a clear imperative of the assessment of an alternative treatment strategy.

As several studies [11-14] have suggested a relative chemo resistance for SRC tumours and delay in definitive surgery may favour tumour progression [8] we hypothesise that a policy of primary surgery for SRC tumours, followed by adjuvant chemotherapy, will improve overall survival at 2 years when compared to a standard peri-operative chemotherapeutic strategy. This primary outcome criteria is justified as it provides a short term evaluation criteria (important in view of the very poor prognosis associated with this disease) and survival at 24 months has been found in a multicentre retrospective series of over 1000 patients to be significantly different (27% vs. 10%) [8].

This randomised trial will provide high level evidence regarding the value of a strategy of primary surgery for SRC gastric tumours. Whilst the development of new biomarkers and associated targeted therapies are awaited to individualise gastric cancer therapy, the results of this trial should will help further in devising individualised protocols of patient care in a tumour group whose diversity increasingly demands assessment of alternative strategies.

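### The target of 291 deaths from 314 patients relies on survival follow-up to the final cut-off, but the protocol follows participants for only 3 years, so the target will probably be narrowly missed

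*Protocol article*

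**What the plan says.** In the protocol article, *Statistical evaluation and sample size calculation* plans phase III to detect a gain of 10 percentage points in 24-month survival for group B. The event target reads: "with a bilateral alpha error of 5% and a power of 85%, it will be necessary to observe 291 deaths". Recruitment is set at 6 patients per month, and 5% of patients are allowed for as losses. The resulting number is given as: "surveillance of the last included patient of 24 months, a total of 314 patients will have to be recruited". The 314 are the 84 phase II patients plus 230 more.

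*Patient follow-Up after surgery* states: "All participants will subsequently be followed for 3 years after randomisation". Visits are every 4 months with examination, CT, tumour markers and quality-of-life questionnaires. No collection of vital status after that period is mentioned.

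*Endpoints of trial* counts death from any cause and censors patients lost to follow-up at their last follow-up date. *Protocol overview* gives a 6-month recruitment pause after phase II and a total study duration of 10 years.

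**The concern.** A target of 291 deaths among 314 patients needs 92.7% of everyone randomised to have an observed death. A calculation with staggered entry and 24 months after the last inclusion counts deaths among early patients well beyond their third year. If observation of each patient ends at 3 years, those late deaths are not recorded. Once the last patient has passed 3 years, no further deaths can be added however long the team waits. Phase III power is stated for 291 deaths, and the text gives no rule for what happens if they do not occur. The timing of the final analysis would then have to be settled late, with data already accumulated.

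**Working it through.** **Inputs.** Two-sided alpha 5%, power 85%, 10-point difference at 24 months, 6 patients per month, 5% loss, 24 months after the last inclusion, N = 314 (*Statistical evaluation and sample size calculation*). 6-month pause (*Protocol overview*). 3 years per participant (*Patient follow-Up after surgery*). Control survival at 24 months of 10% (*Discussion*); *Background* gives 12.3% for the same cohort. Assumptions: exponential survival, 1:1 allocation in phase III, and 20% in group B, inferred as 10% plus 10 points.

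**Reproducing 291.** HR = ln(0.20)/ln(0.10) = 0.699. Freedman: (1.960 + 1.036)² × ((1 + 0.699)/(1 − 0.699))² = 286 deaths. An assumed inflation of about 2% for the interim look gives about 292, close to 291. Schoenfeld's formula gives 280. Other pairs 10 points apart fit worse: 11%/21% needs 299 to 305, and 12.3%/22.3% needs 322 to 328. So 10%/20% is the pair implied.

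**Reproducing 314.** With follow-up open until 24 months after the last inclusion, the first patient is observed for 313/6 + 6 + 24 = 82.2 months. The N that gives 291 expected deaths is 310 with 5% loss as censoring, or 303/0.95 = 319 with simple inflation. These bracket 314. With follow-up stopped at 36 months the same calculations give 317 to 320 and 327 to 330.

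**Deaths expected from 314 under 3-year follow-up.** The monthly death hazards are ln(10)/24 = 0.0959 and ln(5)/24 = 0.0671. The loss hazard is −ln(0.95)/24 = 0.0021. With death hazard λ, loss hazard η and follow-up f, the probability of an observed death is λ/(λ + η) × [1 − exp(−(λ + η)f)].

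- No loss, f = 36: 1 − 0.0316 = 0.968 and 1 − 0.0894 = 0.911, mean 0.9395; × 314 = 295.0.
- 5% loss, f = 36: 0.950 and 0.889, mean 0.919; × 314 = 288.6.
- 5% loss, cut-off 24 months after the last inclusion (patients from the final year have 24 to 36 months): 286.0.

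**Chance of reaching 291** (simulated, 10%/20%; the ranges cover separate simulation runs):

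| Follow-up | Loss | Expected deaths | P(≥ 291) |
|---|---|---|---|
| Open, to 24 months after last inclusion | 5%, censored | 295 | about 88% |
| 3-year limit, same cut-off | 5%, censored | 286 | 18–20% |
| 3-year limit, all complete 36 months | 5%, censored | 289 | 36–39% |
| 3-year limit, same cut-off | none | 292 | 65–66% |
| 3-year limit, all complete 36 months | none | 295 | 86% |

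The 39% comes from spreading the losses uniformly over follow-up; exponential loss gives 36 to 37%. Extending the pause from 6 to 30 months hardly changes the results.

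**Power.** By Schoenfeld, power = Φ(√d/2 × 0.358 − 1.960). This gives 86.3% at d = 291, 86.1% at 289 and 85.7% at 286.

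**Interim.** 60% of 291 = 174.6, that is 175 deaths, far below any of the totals above.

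**The case against.** The strongest defence is that the 3-year sentence describes a visit schedule. It introduces 4-monthly examinations and CT scans, the overall survival definition censors only patients who are lost, and the study is planned for 10 years. Accrual of 314/6 = 52.3 months, the 6-month pause and 36 months for the last patient total 94.3 months, so 10 years leaves room. If vital status were collected to 10 years, about 305 deaths would be expected and 291 would almost certainly be reached. It is also fair that an article condenses a fuller protocol. All this makes the intention uncertain, but it does not remove the conflict. The printed sentence says participants are followed for 3 years, and neither the censoring rule nor the study duration states that survival is collected beyond that. The planned readjustment after phase II may change N, but it leaves the two statements as they are.

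Several stronger readings are not supported:

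- **That 10%/20% are the trial's printed assumptions.** No 20% for group B appears. The article prints 27% against 10%, and elsewhere "overall survival at 2 years of 27.1% in the primary surgery group versus 12.3% in patients treated with neoadjuvant chemotherapy".
- **That the 3-year limit alone makes the target unlikely.** Without loss, 291 is still reached in about 65 to 86% of trials. The result depends on adding the protocol's own 5% loss.
- **That 97.6% of evaluable patients must die** (291/298.3, with 298.3 = 314 × 0.95). This assumes that lost patients contribute no deaths. On that model even open follow-up gives only 287 deaths and reaches 291 in 25% of trials, so it does not isolate the effect of the limit.
- **That better survival proves the point.** At 17%/27%, open follow-up also falls short (about 285 deaths, 15%), and the required count would be 393 to 399 rather than 291.
- **That the interim or the final analysis trigger fails.** The interim is safe, and the text never calls the 291st death the trigger for the final analysis.

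**Conclusion.** The conflict is real and its numerical effect is small. Under the implied 10%/20%, exponential survival and 5% loss as censoring, 3-year follow-up falls about 2 to 5 deaths short on average (291 − 289 to 291 − 286). It turns a target met in about 88% of trials into one met in roughly 18 to 37%. The loss of power is under one point, so this is not a finding that phase III is underpowered, nor that 291 deaths are impossible. What is wrong is that the stated count will probably not be met under the printed follow-up, and waiting cannot close the gap. A hazard that falls after 24 months would give fewer late deaths than the exponential model. A control rate of 12.3% with the same 10-point difference would lower the yield under the 3-year limit to 281 to 284 deaths (4 to 11% of trials).

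**What to change.** Reconcile the two sections. Preferably, state in *Patient follow-Up after surgery* that the 3 years apply to scheduled visits and imaging, and that vital status is collected for every patient until the final cut-off. In *Statistical evaluation and sample size calculation*, define that cut-off as the 291st death or a fixed date, whichever comes first. If 3-year follow-up is really intended, restate the expected deaths and the power for it instead.

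The first option needs no extra patients or visits. Its cost is periodic vital-status checks on the few survivors beyond 3 years: under the implied rates, about 3% of group A and 9% of group B. The second option costs only a recalculation, but it accepts fewer deaths than the 291 now stated.

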### Reasons for discontinuing treatment protocol

The treatment protocol may be discontinued for the following reasons: decision of the treating doctor, high grade toxicity, occurrence of a serious adverse effect, disease progression, patient refusal to continue and patient death. In cases where treatment is discontinued, patients will remain within the intention to treat analysis.

### Statistical evaluation and sample size calculation

Phase II– The phase II part of this trial will determine the percentage of patients in the experimental limb of the study (group B) who are alive at 24 months and thus validate the interest pursuing the evaluation of a strategy of primary surgery in a subsequent phase III trial. To demonstrate the interest of the experimental arm of this study, it will be necessary to include 40 in each treatment arm, with a unilateral alpha error of 5% and a power of 85%. Taking into account a 5% level of loss to follow-up, 84 patients will be included in total (42 in each treatment arm). If 7 or less patients are alive after 24 months, then the treatment B will be considered not interesting. Survival data for patients from phase II of this trial will allow for the readjustment of the number of patients required to be enrolled in the phase III trial according to the adaptive trial design.

Phase III – The objective of the phase III trial will be to demonstrate the superiority of group B and the principal outcome criteria will be overall survival. To demonstrate a desired 10% difference in overall survival in favour of group B at 24 months, with a bilateral alpha error of 5% and a power of 85%, it will be necessary to observe 291 deaths. With an estimated rate of inclusion of 6 patients per month, with a 5% rate of loss to follow-up and surveillance of the last included patient of 24 months, a total of 314 patients will have to be recruited. On this basis 230 additional patients will need to be recruited after the completion of phase II.

Two intermediate analyses are planned, one for Phase III sample size read justement and the second one to allow for the early identification of the superiority of group B. The first intermediate analysis of survival data will take place at the end of phase II. The second intermediate analysis will be performed after either 175 deaths or 60% of events have occurred.

Statistical analysis for phase II will be performed on a modified intention to treat population meaning all patients who can be evaluated and who are not lost to follow up at 24 months. For phase III, analysis of the main criteria will be performed on an intention to treat (ITT) principle. The per-protocol population will be defined as the ITT population having no major deviation or major of the protocol.

Continuous variables will be described by their mean and standard deviation or median, Interquartile Interval (Q1-Q3) and range. Survival endpoints will be estimated using the Kaplan Meier method, described by median values with 95% confidence Interval and compared in Phase III using the log-rank test. QoL data will be analysed according to treatment arm and treatment tolerance assessed using the National Cancer Institute Toxicity Criteria – (NCI CTC). The Clavien-Dindo scale will be used to assess peri-operative complications [16]. Cox univariate and multivariate analyses will allow exploratory analyses of prognostic factors, time until deterioration of QoL and disease free survival.

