**Methods/design:**

PRODIGE-19-FFCD1103-ADCI002 is a prospective multicentre controlled randomised phase II/III trial comparing current standard of care of perioperative chemotherapy (2x3 cycles of Epirubicin, cisplatin, 5-fluorouracil) with a strategy of primary surgery followed by adjuvant chemotherapy (6 cycles of Epirubicin, cisplatin, 5-fluorouracil) in patients with a stage IB-III gastric signet ring cell tumour. The principal objective of the phase II study (84 patients) is to determine if the experimental arm (primary surgery followed by adjuvant chemotherapy) has sufficient interest in terms of percentage of living patients at 24 months to be evaluated in a phase III trial. If 7 or less patients in the experimental arm are alive at 24 months, phase III will not be initiated. The primary objective of phase III (230 additional patients) is to demonstrate superiority of the experimental arm in terms of overall survival. Secondary endpoints include overall survival at 36 months, disease free survival at 24 and 36 months, R0 resection rates, treatment tolerance, postoperative mortality and morbidity evaluated by Clavien-Dindo severity index, the prognostic impact of positive peritoneal cytology and the assessment of quality of life. An ancillary study will assess the emotional and cognitive impact of surgery and perioperative chemotherapy for both the patient and their partner.

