## Methods/design

### Protocol overview

PRODIGE-19-FFCD1103-ADCI002 is a prospective multicentre controlled randomised phase II/III trial comparing current standard of care (2x3 cycles of perioperative Epirubicin, cisplatin, 5-fluorouracil (ECF) chemotherapy) with a strategy of primary surgery followed by adjuvant ECF chemotherapy (6 cycles) in patients with a SRC tumour and eligible for curative surgery. In phase II patients will be randomised using minimisation with stratification criteria – centre, tumour stage, performance status and tumour localisation. The principal objective will be to determine if the experimental arm (primary surgery followed by adjuvant chemotherapy) has a sufficient interest in terms of percentage of living patients at 24 months to be evaluated in a phase III trial. If ≤10% of patients in the experimental arm is alive at 24 months, phase III will not be initiated. Recruitment will be postponed for a 6 month period after the completion of phase II of the study to allow for the interim analysis of data. The primary objective of phase III will be to demonstrate the superiority of the experimental arm in terms of overall survival. The study is planned for a total duration of 10 years and is registered on clinicaltrial.gov website (NCT01717924).

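### The phase II gate is powered for about 26% alive in group B, while phase III's 291 deaths fit about 10% versus 20%; at that target the chance of passing both is about 52-58%

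*Protocol article*

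**What the plan says.** All design figures are in the protocol article, mainly under Statistical evaluation and sample size calculation.

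- **Phase II size:** "it will be necessary to include 40 in each treatment arm, with a unilateral alpha error of 5% and a power of 85" percent. Enrolment is then raised for losses: "Taking into account a 5% level of loss to follow-up, 84 patients will be included in total (42 in each treatment arm").
- **Phase II analysis set:** "all patients who can be evaluated and who are not lost to follow up at 24 months".
- **Gate:** "If 7 or less patients are alive after 24 months, then the treatment B will be considered not interesting". The abstract has the same cut-off: "If 7 or less patients in the experimental arm are alive at 24 months, phase III will not be initiated".
- **Gate in the Protocol overview:** worded differently, "If ≤10% of patients in the experimental arm is alive at 24 months, phase III will not be initiated". This is the only place where a 10% rate is tied to the gate.
- **Phase III:** "To demonstrate a desired 10% difference in overall survival in favour of group B at 24 months, with a bilateral alpha error of 5" percent and "a power of 85%, it will be necessary to observe 291 deaths". The total is 314 patients, of whom 230 are recruited after the 84 of phase II.

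No alternative rate is printed for phase II and no control rate for phase III. The retrospective cohort cited as justification is given as 27.1% versus 12.3% in the Background and as 27% versus 10% in the Discussion. Power is quoted for each phase separately; no figure is given for the two phases together.

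**The concern.** The phase II patients count towards the 314 patients and 291 deaths of phase III, and phase III opens only if the gate is passed. A real benefit is therefore found only if both steps succeed. If the gate is tuned to a larger group B survival than phase III is sized to detect, a benefit of exactly the size phase III looks for will often be discarded before phase III begins. A reader who sees 85% beside each phase would not notice this.

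**Working it through.** **1. What the gate is powered for.** Inputs: 40 evaluable in group B, continue if 8 or more are alive, one-sided 5%, power 85% (sample size section); null 10% (Protocol overview). With X ~ Binomial(40, p):

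- P(X ≥ 8 | p = 0.10) = 4.19%, within the stated 5%.
- P(X ≥ 8 | p = 0.26) = 85.3%; power crosses 85% at p = 25.9%.
- The smallest exact single-stage design is n = 40 with cut-off 7 for 10% versus 26%, n = 47 for 10% versus 25%, and n = 34 for 10% versus 27%.

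The printed design is therefore reproduced by 10% versus 26%. Testing 10% versus 20% at the same error rates would need n = 93.

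**2. What phase III is sized for.** Inputs: 10-point gain at 24 months, two-sided 5%, power 85%, 291 deaths. Under exponential survival HR = ln(p_B)/ln(p_A), and (1.960 + 1.036)² = 8.98.

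- Freedman: deaths = 8.98 × [(1 + HR)/(1 − HR)]².
- Schoenfeld: deaths = 4 × 8.98/(ln HR)².

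| A versus B | HR | Freedman | Schoenfeld |
|---|---|---|---|
| 10% vs 20% | 0.699 | 286 | 280 |
| 12.3% vs 22.3% | 0.716 | 328 | 322 |
| 16% vs 26% | 0.735 | 385 | 379 |

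Solving for exactly 291 puts group B at 20.3% (Freedman) or 20.6% (Schoenfeld). A second solution near 60% versus 70% is excluded: with 6 patients per month and 24 months of follow-up for the last patient, 314 patients would then yield only about 181 deaths. At 10% versus 20% they yield about 302, or 287 after 5% loss.

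**3. The gate at phase III's target.** P(X ≥ 8) at p = 0.20 is 56.3% with 40 evaluable and 62.2% with 42, so the trial stops 43.7% or 37.8% of the time. At 20.3-20.6% with 40 evaluable it still stops 40-42% of the time.

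**4. Both steps together.** The trial was simulated with exponential survival, 42 patients per arm from phase II pooled with 230 more, the gate on group B, and a two-sided 5% log-rank test at the 291st death.

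| True A versus B | Gate passed (40 / 42 evaluable) | Phase III alone | Both |
|---|---|---|---|
| 10% vs 20% | 56% / 62% | about 86% | about 52-58% |
| 12.3% vs 22.3% | 70% / 75% | about 81% | about 59-64% |
| 10% vs 27% | 88% / 91% | over 99% | about 88-91% |
| 12.3% vs 27.1% | 89% / 92% | about 98% | about 87-90% |

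A hand check on the first row: joint success cannot exceed the pass probability (56.3% or 62.2%). If the two steps were independent it would be 0.563 × 0.856 = 48% or 0.622 × 0.856 = 53%. Shared patients make the steps positively correlated, so the answer lies between these values. The same ceiling shows why readjusting the phase III sample size cannot recover the loss.

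**5. The other gate wording.** Read as an observed proportion, 10% of 40 is 4 patients. Stopping at 4 or fewer passes a true 20% with probability 92%, and joint success is about 79-81%. However, P(X ≥ 5 | p = 0.10) = 37%, which does not fit the stated 5%. A cut-off of 7 of 40 is 17.5%. Only the rule of 7 matches the printed error rates.

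**The case against.** The strongest defence is that the gate was set at the survival the investigators expected and phase III at a smaller difference still worth finding. An alternative of about 26% sits close to the cohort's 27%, and at the cited cohort rates the whole trial keeps about 87-91% power. That stands. It means the design does not fail under its own motivating evidence.

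Two further points also stand. Both 26% and 20% are back-solved, and 10% versus 20% gives 280-286 deaths rather than exactly 291. The article also condenses a fuller protocol that may print these rates. Neither removes the mismatch, because the printed cut-off, error rates, effect and event count fix the rates closely enough.

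A reader might infer more than the document supports in two ways:

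- **That a stated whole-trial power of 85% is false.** The article gives 85% per phase and makes no joint claim. The low joint figure is an undisclosed consequence, not a contradicted number.
- **That the gate must be changed to compare group B with group A.** Phase II is defined as estimating group B's percentage alive, and passing it is no claim of efficacy; phase III's two-sided test decides that. A non-binding comparison is an option, but any hazard-ratio limit would be a matter of preference, and an added stop could not raise joint power.

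**Conclusion.** The concern holds as a mismatch between the alternatives of the two phases. At the 10-point target that fits 291 deaths, the gate stops the trial about 38-44% of the time, and the chance of passing it and then winning phase III is about 52-58%. With a 12.3% control rate it is about 59-64%. At the cited cohort rates it is about 87-91%.

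These figures assume a 10% null, exponential survival, 40 to 42 evaluable group B patients and the rule of 7. They ignore the alpha spent at the interim superiority analysis, which would lower power slightly. If the 10% wording in the Protocol overview were the operative rule, joint power would be about 79-81%, but the stated 5% error rate would not hold.

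**What to change.** 1. Under Statistical evaluation and sample size calculation, print the null and alternative behind the phase II cut-off and the two survival rates behind the 291 deaths.
2. In the same place, say that phase III's 85% is conditional on passing the gate. Give the joint power for the 10-point target (about 52-58% if that is 10% versus 20%) beside that for the cited cohort rates (about 87-91%).
3. Reconcile the 10% gate in the Protocol overview with the rule of 7 in the abstract and the sample size section, so that one cut-off is stated throughout.

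The cost is a few sentences and a less favourable power statement; no patient numbers change. Disclosure does not itself raise the joint power. If the sponsor wants more at 20%, the gate must be redesigned: 10% versus 20% at the phase II error rates needs 93 evaluable patients in group B. A non-binding comparison with group A at the phase II look is optional and not part of this correction.
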